|                                                   | 
 
• duration of participation (treatment + follow-up): 28 days
 
• Total duration: 19 months
 
• Duration of prohibition from participation in other research and rationale: No prohibition from participating in other intervention research
 
                                                                                                                                                                                                                                                                                                                                                                                                                                                                                                                                                                                                                                                                                                                                                                                     |
| Number of planned inclusions per centre per month | At least 4 patients per department per month and more if possible                                                                                                                                                                                                                                                                                                                                                                                                                                                                                                                                                                                                                                                                                                                                                                                                                                                                                                                                                                                                                               |

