# **3 RESEARCH OBJECTIVES**

## **3.1 Main objective of the research**

To show that daily prone positioning (objective of at least 6 hours/day) in COVID-19 patients with respiratory failure requiring oxygen therapy of at least 3L/min to obtain a saturation  $\geq 95\%$  reduces the proportion of patients requiring intubation and/or death.

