#### **8.2.2 Stopping part or all of the research**

The promoter AP-HP reserves the right to permanently suspend inclusions, at any time, if it turns out that the inclusion objectives are not achieved.

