### ***Main criterion:***

The posterior probabilities of the primary endpoint will be calculated using different types of priors (non-informative or vague).

The following posterior probabilities will be calculated:

P (OR>1), corresponding to a non-zero effect of the prone position.

P (OR>1.05) corresponding to an effect that is already clinically interesting.

P (OR<1) corresponding to inefficiency of the prone position.

P (OR < 0.95) corresponding to a deleterious effect of the prone position.

The thresholds considered particularly interesting for the a posteriori probabilities described below are respectively equal to 0.95, 0.80, 0.8, 0.75.

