### ***Statistical criteria for stopping the search.***

Interim analyses will be done every 50 patients (followed up to the primary endpoint).

The study may be stopped for efficacy after the 2nd interim analysis, if one of the 2 conditions below is met:

P( OR>1) >0.95

P (OR>1.05) >0.8

The study may be stopped after the 2nd interim analysis for safety if P (OR< 0.95) >0.75

The study may be stopped for futility after the 4th interim analysis

P( OR>1) < 0.1

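### The only statistical safety rule in section 13.1 uses the efficacy composite, so excess deaths after intubation, or offset by fewer intubations, do not move it

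*Protocol*

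**What the plan says.** Under the heading on statistical stopping criteria in section 13.1, the Protocol sets the schedule: "Interim analyses will be done every 50 patients (followed up to the primary endpoint"). From the second look it allows an efficacy stop if P(OR>1) exceeds 0.95 or P(OR>1.05) exceeds 0.8. The safety rule is: "The study may be stopped after the 2nd interim analysis for safety if P (OR< 0.95) >0.75". A futility rule follows from the fourth look.

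The main-criterion paragraph of 13.1 says which outcome the odds ratio describes: "The posterior probabilities of the primary endpoint will be calculated using different types of priors (non-informative or vague"). It also gives the direction: "P (OR < 0.95) corresponding to a deleterious effect of the prone position". An OR above 1 therefore favours prone positioning. The main objective in section 3.1 is to show that prone positioning "reduces the proportion of patients requiring intubation and/or death", and section 4.1 assesses the composite up to day 28.

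Other provisions on stopping and safety:
- Section 8.2.2 lets the sponsor suspend inclusions "if it turns out that the inclusion objectives are not achieved".
- Section 15.3 lets the sponsor interrupt the research at any time on medical or administrative grounds.
- Section 10 states that adverse events, serious or not, are not reported to the sponsor.
- Section 11 describes only a steering committee.
- Section 6.1.2 has vital status read daily for up to 28 days, with a telephone call for patients discharged earlier.

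**The concern.** The safety rule and the efficacy rule read the same statistic from opposite ends. Intubation is the event that prone positioning is meant to avoid, and it may make up much of the composite. Two patterns of excess death are then invisible to the safety rule. A patient who dies after intubation was already counted at intubation. A death balanced by an avoided intubation leaves the count unchanged.

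If prone positioning avoided or postponed intubations while deaths rose, the safety probability would fall and the efficacy probability would rise. The trial could stop early and report benefit on the composite while its own data pointed to more deaths. No written rule requires anyone to look at deaths before that stop.

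**Working it through.** **1. The design figure.** The maximum of 500 rests on 25% vs 15% with 80% power (section 13.1). The alpha level is not stated; 5% two-sided is assumed.

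n per arm = [1.96 × √(2 × 0.20 × 0.80) + 0.8416 × √(0.25 × 0.75 + 0.15 × 0.85)]² / 0.10² = (1.1087 + 0.4724)² / 0.01 ≈ 250, or 500 in total. The stated figure reproduces, so 25% vs 15% is used below.

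**2. Patients enrolled when the safety rule can first act.** The second look needs 100 patients with 28 days completed. The Protocol describes no pause in recruitment, so enrolment is taken to continue.

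Enrolled = 100 + monthly accrual × 28/30.44.
- 500 patients in 18 months (section 7.3) is 27.8 per month: 100 + 25.6 = 125.6, about 126.
- The synopsis gives 21 centres and "At least 4 patients per department per month and more if possible". Taking a department as a centre, this is 84 per month: 100 + 77.3 = 177.3, about 177.

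The two accrual figures disagree (84 × 18 = 1,512, not 500), so both are shown. The 84 is a stated minimum, so 177 is not an upper bound. If the wording means from the third look onward, the range is about 176 to 227.

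**3. What moves the safety rule.** Take look 2 with 50 per arm and 10 control events (Jeffreys priors assumed):

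| Prone events | P(OR<0.95) |
|---|---|
| 10 | 0.46 |
| 13 | 0.74 |
| 14 | 0.80 |

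Four extra deaths in non-intubated prone patients would cross 0.75. With 10 events in each arm the value stays at 0.46, however many of the prone events are deaths.

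**4. How often an efficacy stop could coincide with probable excess death.** The method was 20,000 simulated trials per scenario, with looks at 25 more patients per arm up to 250 per arm. The efficacy and safety rules of section 13.1 were applied from look 2. Assumptions: 1:1 allocation, Beta(1,1) priors, and a normal approximation to the log-OR posterior. Deaths are a subset of composite events. The Protocol gives no death rates, so those below are assumptions.

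With the composite at 25% control vs 15% prone, trials stop for efficacy in about 96% and for safety in about 2.8%. These two figures do not depend on deaths. The share of all trials that stop for efficacy while the posterior probability of excess death with prone is above 0.90 does:

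| Deaths, control vs prone | Share of events that are deaths, control vs prone | Efficacy stop with P(excess death) > 0.90 |
|---|---|---|
| 5% vs 10% | 20% vs 67% | about 33% |
| 10% vs 15% | 40% vs 100% | 24% |
| 5% vs 7.5% | 20% vs 50% | 17% |
| equal | – | about 5% |

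The 10% vs 15% row is extreme: every prone event is a death.

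**5. Cost of a death criterion.** The last row gives the cost of holding an efficacy stop at 0.90: about 5% of trials with equal deaths would be delayed. A separate pause trigger at 0.95 for death, applied at all ten looks, fires at least once in about 11% (deaths 5% in both arms) to 14% (10% in both) of trials run to 500. At look 1 alone it fires in 0.2% to 1.6% of trials with no effect on death. It detects harm there in only about 4% (5% vs 10%) to 7% (10% vs 15%).

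**The case against.** A reader might infer that an excess of deaths can never trigger the safety rule. The document does not support that. Death is a component of the composite, so excess deaths without intubation do count. With a 20% control rate, if such deaths raise the prone rate to 30%, the rule is met at look 2 in about 64% of trials. It is met in about 22% even with no effect. It is not an insensitive rule for harm on the composite.

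A reader might also infer that no harm stop is possible before the second look. That is not supported either. Section 15.3 allows interruption at any time for medical reasons, section 8.2 allows an individual's participation to be ended for safety, and section 10 keeps the duty to inform the authority and the ethics committee of new facts. This objection stands. What remains is that none of these routes names a mortality criterion, and section 10 gives the sponsor no adverse event reports on which to use the section 15.3 power.

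Waiting for 100 followed patients is a defensible choice when events are few. It applies equally to efficacy, and step 5 shows how little a death trigger would detect at 50 patients. The absence of a rule at the first look is therefore not pressed here.

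The masking scenarios are assumed, and two of them are strong. The milder case still gives 17%, against about 5% with equal deaths. Finally, a SAP or monitoring document might add a mortality review. Section 13.1, however, already sets out the stopping criteria with their thresholds, and as written they permit an efficacy stop without any reference to deaths.

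**Conclusion.** The point holds as a weakness in the design of the stopping rules; it is not a contradiction in the text. The only statistical safety rule is the opposite tail of the efficacy statistic. It sees excess deaths without intubation, but not those that follow intubation or are offset by fewer intubations. In the latter case the efficacy rule can stop the trial.

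Under the assumed death rates, between 17% and 33% of trials would stop for efficacy while excess death was probable at the 0.90 level. These figures rest on the assumed deaths, priors and allocation, and show scale only. The 126 to 177 enrolled at the first permitted safety stop follow from the Protocol's own accrual figures. They assume that recruitment continues, that the second look itself is included, and that data entry causes no lag. They describe the statistical rule only, because the sponsor's general power to interrupt applies throughout.

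**What to change.** In section 13.1:
- At every look, also compute the posterior for death by day 28, from the vital status already collected under section 6.1.2.
- State that no efficacy stop is made while the posterior probability of excess death with prone exceeds a pre-set level (for example 0.90), with the level fixed by simulation.
- Describe the P(OR<0.95) criterion as a harm rule on the primary composite.

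The cost is wording and one more posterior per look, with no new data, staff or patients. About 5% of trials with no effect on death would have an efficacy stop delayed.

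If the sponsor also wants a death-based pause-and-review trigger, the Protocol should state its cumulative false-pause rate over all looks (about 11% to 14% at 0.95 over ten looks), not the look-1 rate. Whether any trigger should act at the 50-patient look is for the sponsor to decide.

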### ***Method of accounting for missing, unused or invalid data***

All patients included in the database will be analyzed. The reasons for leaving the study and/or protocol violations will be described for each group. An analysis of patients who have followed the protocol without major violations will be done (per-protocol analysis). It will be considered secondary. For analyses requiring full data in a patient, two analyses will be performed, one on the actual available data, the other using a multiple imputation replacement procedure. The robustness of the

conclusions will be verified, and any discrepancies will be analyzed according to the data collection biases that may have been identified.

### ***Manage changes to the initial strategy analysis plan.***

In the event of changes to the criteria described in the protocol, a specific statistical analysis plan will be drawn up before any unblinding.

### ***Population Selection***

All randomized patients will be analyzed in ITT

A per-protocol analysis on all randomized patients without major violations will be done and considered secondary. A secondary analysis will also be performed according to the duration of the prone position. If the difference between the ITT population and the PP population is < 10%, only the ITT analysis will be performed.

## **14 QUALITY CONTROL AND ASSURANCE**

### **14.1 General organization**

The sponsor must ensure the safety and respect of the individuals who have agreed to participate in the research. It must set up a quality assurance system to monitor the progress of research in the investigator centres as well as possible.

To this end, the promoter will define a strategy for opening up the centres and may, if necessary, set up a data quality control.

These notions will be adapted throughout the confinement period.

#### **14.1.1 Strategy for opening up centres**

The strategy for opening the centres will be determined before the start of the research.

#### **14.1.2 Data quality control**

In the context of the COVID-19 pandemic, the usual rules for tracking searches cannot be followed. The confinement decreed by the government imposes a degraded operation of the research that is about to begin (APHP promoter), among other things, the impossibility of carrying out monitoring visits on site.

The following procedure aims to define a course of action to be taken in order to adapt the monitoring rules in accordance with rights, the safety of people and the quality of data, always in accordance with the regulations in force. These actions to be taken are defined according to the risk and the level of monitoring of this study, of which the APHP is sponsoring.

This *modus operandi* will no longer be applied once the confinement period is over.

A Clinical Research Associate (CRA) mandated by the sponsor will ensure that the research is carried out properly by adapting it to the current working conditions (confinement), and to the risk of the study

- Obtaining compliant consents
- Advancing recruitment in research
- Safety of people included in the research
- Update on compliance with the protocol

- A strategy for reporting non-conformities (consent and follow-up of recruitment) will be put in place

The investigator and the members of his team agree to make themselves available during the Quality Control visits carried out by telephone at regular intervals by the Clinical Research Associate.

## 14.2 Case Report Book

The case report form contains only the data necessary for analysis for publication. All the data relating to the subject and necessary for his follow-up during and outside the research will be collected in his medical file.

### Paper CRF:

All the information required by the protocol must be recorded in the case report forms and an explanation must be provided for each missing data. The data will have to be collected as they are obtained, and transcribed in these notebooks in a clear and legible way.

Erroneous data found in the case report forms will be crossed out and the new data will be copied, next to the crossed out information, accompanied by the initials, the date and possibly a justification by the investigator or the authorized person who made the correction.

### Electronic FIU :

All information required by the protocol should be recorded in the case report forms. Data will need to be collected as they are obtained, and recorded in these notebooks explicitly. Each missing data will have to be coded.

This electronic observation notebook will be set up in each of the centres using an Internet data collection medium. A guidance document for the use of this tool will be provided to investigators.

The investigator is responsible for the accuracy, quality, and relevance of all data entered. In addition, when they are entered, this data is immediately checked for consistency. In this regard, the investigator must validate any change in value in the CRF. These changes are subject to an audit trail. A justification may be included in the commentary.

A paper printout will be requested at the end of the study, authenticated (dated and signed) by the investigator. The original of this document will be archived by the proponent. A copy of the authenticated document should be archived by the investigator.

## 14.3 Non-conformance management

Any event occurring as a result of non-compliance with the protocol, standard operating procedures, or applicable laws and regulations by an investigator or any other person involved in the conduct of the research must be declared non-compliant to the sponsor.

These non-conformities will be managed in accordance with the proponent's procedures.

## 14.4 Audit

The investigators undertake to accept the quality assurance audits carried out by the sponsor as well as the inspections carried out by the competent authorities. All data, documents and reports can be audited and regulated without medical confidentiality being invoked.

An audit may be carried out at any time by persons mandated by the sponsor and independent of the research managers. Its objective is to ensure the quality of the research, the validity of its results and compliance with the law and regulations in force.

Individuals who direct and monitor the research agree to comply with the sponsor's requirements for an audit

The audit may apply to all stages of research, from the development of the protocol to the publication of the results and the classification of the data used or produced in the research.

#### **14.5 Commitment of responsibilities of the Principal Investigator**

In the current conditions of confinement and overload of work in the care services, it will be accepted to have available at the beginning of the study a CV dated more than one year, unsigned and/or undated to be updated by each investigator as soon as this period is lifted. The same goes for training courses related to clinical research.

Each investigator will undertake to comply with legislative and regulatory obligations and to conduct research in accordance with the regulations, in accordance with the terms of the Declaration of Helsinki in force.

The principal investigator of each participating centre will sign a commitment of responsibilities (DRCI type document) which will be given to the sponsor's representative.

Investigators and their collaborators will sign a delegation of duties form specifying the role of each and provide their CV.

### **15 ETHICAL AND LEGAL ASPECTS**

#### **15.1 Procedures for informing and obtaining the consent of persons participating in the research**

In accordance with Article L. 1122-1-1 of the Public Health Code, no research involving a human person with a risk and minimal constraint may be carried out on a person without his or her free and informed consent, and expressly after the information provided for in Article L. 1122-1 of the same Code has been delivered.

A reflection period adapted to the COVID-19 pathology will be given to the person between the time he or she is informed and the time he or she signs the consent form, as the positioning must begin as soon as possible.

The free, informed and written consent of the person is obtained by the principal investigator, or by a doctor who represents him/her, before the inclusion (before any research-related acts) of the person in the research, and this as early as possible in the COVID patient care department (list of participating centers in addendum) on presentation of the written information note and oral explanations.

After both parties have signed, the person will keep the briefing note describing the research and the consent and the principal investigator or the physician representing them will keep a copy of the consent signed by the person. The briefing note is available throughout the research in the investigator workbook. It will be updated in the workbook if it changes.

A copy will be placed at the end of the study in a sealed tamper-proof envelope containing all the consent forms, which will be archived by the sponsor.

In addition, the investigator will specify in the person's medical record the person's participation in the research, the procedures for obtaining his or her consent and the procedures for providing the information for the purpose of obtaining it. He or she keeps a copy of the form for the collection of consent of the person, dated and signed.

### **15.2 Prohibition on participation in any other research or exclusion period provided for at the end of the research, if applicable**

During the period of participation in the research, the patient may participate in another research protocol involving the human person. The latter, included in this study with minimal risks in COVID services, are asked to participate in several protocols. The principal investigator or his representative will verify that participation in two research projects at the same time is without any interaction with each other while ensuring maximum patient safety, in order to advance the research as quickly as possible.

Patients will also be able to participate in other non-interventional research, if they agree.

### **15.3 Legal obligations**

The Assistance publique hôpitaux de Paris (AP-HP) is the promoter of this research and by delegation the Clinical Research and Innovation Department (DRCI) carries out its missions, in accordance with Article L.1121-1 of the Public Health Code. Assistance Publique - Hôpitaux de Paris reserves the right to interrupt the research at any time for medical or administrative reasons; in this case, a notification will be provided to the investigator

### **15.4 Request for an opinion from the Committee for the Protection of Persons CPP**

The AP-HP, as a sponsor, obtains the favourable opinion of the CPP concerned for intervention research with minimal risks and constraints, prior to its implementation, within the framework of its competences and in accordance with the legislative and regulatory provisions in force.

